## 5. TREATMENT OF SUBJECTS

At MMC, the current device used for conventional CTG monitoring is the Philips Avalon FM 30 (Philips Healthcare, Eindhoven, the Netherlands). The FHR is measured non-invasively by DU. The uterine activity and maternal heartrate are monitored by TOCO.

### 5.1 Investigational treatment

All patients will receive routine care following national guidelines and/or local protocols. Participants at the clinic will receive self-administered remote eCTG monitoring by NRM once a day (*Figure 1*). In case of follow-up at the outpatient clinic, participants will receive self-administered remote eCTG monitoring by NRM once per day or at least twice a week, depending on their care path. The realtime eCTG measurement will be instantly transferred digitally to the hospital electronic patient file (Chipsoft HiX) and assessed real-time on interpretability by the HCP. Monitoring will last between 30-90 minutes depending on the interpretability and reassurance of the remote eCTG measurement. Criteria defining a successful measurement are described in a standard operating procedure (SOP) and will be available for HCPs at the hospital to avoid prematurely closing of the eCTG measurement (see section 7.1.1). All HCPs involved in this study will receive training on the study protocol. The study procedure and statistical analysis are described in section 7.3.2, chapter 9 and in *Figure 12*.

Monitoring will be repeated the same day when reassuring but insufficiently interpretable, or upon request of the HCP in case of concerns about maternal and/or fetal condition. Additional detailed information of the NRM is described under investigational product (chapter 6). When remote eCTG interpretability is insufficient – based on clinical assessment of HCPs – a switch to conventional CTG monitoring will take place. In this study, HCPs will be asked to define clearly if a switch to conventional CTG was made based on insufficient interpretability or because of concerns about fetal and/or maternal condition (section 7.1.2).

From the second day onward, synchronized US Doppler measurements (clips of 2 x 5 minutes) of the umbilical and uterine arteries will be performed simultaneously with the remote eCTG for 24 patients ([images removed]

*Figure 3*). Measurements of two groups - cardiovascular low (PPROM; N=12) versus cardiovascular high-risk (PE/FGR; N=12) - will be collected and analyzed to evaluate the feasibility of synchronized multimodal acquisitions of maternal and fetal measurements.

[images removed]

*Figure 3. Measurement fetal and maternal heartrate, Doppler arteria umbilicalis, Doppler uterine artery and uterine activity.*

During routine hospital care, admitted patients are asked daily for possible symptoms, and vital functions (e.g. heartrate, blood pressure, temperature, fluid balance) will be collected. During the study, the participants of this Home@Hospital study will measure their own vital functions, since this would also be the case when they were in a true Hospital@Home setting. Patients will therefore also register their vital functions and symptoms (e.g. PE-symptoms, abdominal pain, contractions, blood loss and fetal movements) during all remote ECTG measurements, this is done in the Luscii® app on

their telephone or tablet. The Luscii® app is widely used in the Netherlands and is already implemented in MMC as regular clinical care. For pregnancy, a separate function is available in Luscii® which will be used in the HASTA study (*Figure 4*). For a more detailed description of procedure interventions, see section 7.3.2.

To assess wellbeing and satisfaction, participants will receive questionnaires through email by Research Manager® at inclusion, discharge and 4 weeks postpartum (see description in sections 7.3.3 and 9.2.1). To assess HCP satisfaction, all HCPs involved in the HASTA study will receive a digital questionnaire – through mail by Research Manager® – once the last participants has delivered or has reached the GA of 37 weeks. Survey is based on a validated patient questionnaire (31) and suitable for HCPs after minimal adjustments. The validated survey is attached to appendix B. For further description and analysis of the questionnaires (see sections 7.3.6 and 9.2.1)

[figure not shown]

*Figure 4. The Luscii app®*

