## **2. OBJECTIVES**

### **2.1 Primary objective**

The primary objective of this study is to assess the percentage of successful self-administered remote eCTG (including NI-fECG ) measurements in a Home@Hospital setting. This will be defined based on the percentage of signal loss and total duration of adequate registration and will be assessed on the first or – when indicated – the second eCTG measurement on the first day of inclusion. When the first remote eCTG measurement is reassuring but insufficient, the measurement will be repeated the same day.

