### **2.2 Secondary objective(s)**

The secondary objective is to evaluate the interpretability of eCTG measurements throughout the hospital period as described in section 2.1 and defined in section 7.1.1. In addition – regarding eCTG measurements – will be assessed the number of repeated eCTG measurement the same day – because of insufficient interpretability – including possible causes of poor signal quality, and the number of switches from eCTG to conventional CTG including possible reasons. Furthermore, will be assessed automated interpretation and the effects of self-administered remote eCTG monitoring in a Home@Hospital setting on maternal and perinatal outcomes, patient and HCP satisfaction, and costs.

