#### **4.4 Sample size calculation**

In a previous cohort study for conventional remote CTG monitoring, 4% of all tracings needed repetition (562 out of 12,649) and 0.9% (N=111) of the CTGs had to be repeated in the hospital. The success rate at first trace was 95.5% and after repetition 99% (28) .

A success rate of 90% is considered clinically sufficient based on previous studies (28-30) and HCPs' opinion. Only the first day of remote eCTG measurements will be used for determination of the feasibility by assessing the signal quality and success. If the remote eCTG measurement is technically insufficient but reassuring – according to current clinical policy – it can be repeated once at the same day and still be considered successful. Calculated on 90% chance of success according Wilson standard error of proportions (CI95% > lower limit of 82.5%), 60 subjects are needed for inclusion in this cohort study.

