- The system is developed to detect FHR from extremely small fetal ECG signals in electrical measurements that may contain significant amounts of noise. The system evaluates the quality of the fetal ECG component in the measured signals. When the fetal ECG quality is too low to reliably detect the FHR, the FHR output is suppressed. In case clinical decision-making cannot be sufficiently substantiated, other observation and monitoring methods must be used.
- To prevent incorrect output, the system continuously evaluates the quality of the FHR output. If the FHR output repeatedly has not passed this quality check over a certain period of time, the FHR output is suppressed. In case clinical decision-making cannot be sufficiently substantiated, other observation and monitoring methods must be used.

- The system detects uterine activity based on electrohysterography (electrical activity of the uterine muscle). In limited cases, the registration may show deviations from the baseline that are not related to actual contractions, when compared to an intra-uterine pressure catheter. In case clinical decision-making cannot be sufficiently substantiated, other observation and monitoring methods must be used. Nemo Remote - Technical Brochure 7
- The system only provides qualitative information about uterine activity and no information about pressure.
- The measurement of abdominal fetal ECG, as performed by the system, is based on extremely small signals. For optimum measurement of these signals, the Link contains sensitive components that are subject to technological limitations. To prevent incorrect measurements through external electromagnetic interference, it is recommended to avoid using equipment that emits electromagnetic radiation in the vicinity of these measurements.
- The system shall only be used if the tablet is configured by mobile device management to ensure data privacy and guarantee the performance of the system.

[removed for publication]

*Figure 7. Physical Specifications – Nemo Remote® Link and Link charger*

[removed for publication]

*Figure 8. Physical Specifications. Nemo Remote® App*

[removed for publication]

*Figure 9. Physical Specifications: Nemo Remote® accessories*

[removed for publication]

*Figure 10. Environmental Specifications*

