## **7.3 Study procedures**

### **7.3.1 Selection, counseling and inclusion**

An overview of the study procedure is integrated in the flowchart presented in chapter 3.

Eligible patients are identified at admission or at the outpatient clinic if an indication for monitoring at least twice a week is set (1st day). All eligible patients will be consecutively asked if they agree to receive information about the study by the attending gynaecologist or resident. They will receive verbal and written information (patient information folder (PIF)) in Dutch or English about remote eCTG monitoring in a Home@Hospital setting. The information will be provided by another (trained) attending obstetric health care professional (resident, physician assistant (PA), (research) midwife or nurse). Possible further questions will be answered and counselling will be performed by one of the researchers or their delegates (trained and registered in a delegation log). Procedure as prescribed above, will ensure that patients' participation will not be influenced by a dependent factor. Additionally, a brochure 'Wetenschappelijk onderzoek' will be assigned to the patient in 'mijnmmc' account – available for all patients – to provide general information about participation in scientific research. Patients will have 24 hours to decide if they want to participate in the study. After 24 hours (2nd day) – when still eligible – patient will provide informed consent and will receive a hard copy of the informed consent form. Given the nature of the study and the study population, it is necessary to deviate from standard Dutch regulations where a minimum reflection period of 7 days is required. This study concerns high-risk pregnant women where the delivery can take place within a short period of time (within a few days). In addition, to answer the research question, it is of great importance that fetal monitoring is examined early after diagnosis so the sample size of 60 participants will be achieved. Patients will be free to ask more time to think about it. When they meet the inclusion and exclusion criteria a few days after admission, it is still possible to participate in the study. Patients who are monitored on an outpatient basis have extra time to think about it until the next outpatient appointment if necessary.

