A study number will be created in Research Manager® for every participant. After inclusion, the investigator or HCP will create a patient account through the general HASTA account on the Lusci® platform (see sections 2.2, 5.1). The participant will instantly receive through email an invitation to create a Lusci® account. Once the participant has downloaded the Lusci® app on their tablet or smartphone, users' introduction will start and explain all functionalities. Participants without access to a tablet or smartphone will have the possibility to use the tablet of the NRM.

From the second day onwards, for each inclusion, it is assessed whether the participant fits the aimed profile (section 5.1) and whether the additional measurements are logistically feasible.

Participants will be asked if they agree to the additional measurements described in sections 2.3 and 7.1.3.

Patients who decide not to participate will receive standard care which consist in conventional CTG monitoring, measurements will be done by HCP and patients will not register their measurements and symptoms in the Luscii® app.

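### Recordings made during Doppler scanning are pooled with self-administered ones in the secondary eCTG results, and the Doppler start day is not anchored to the primary recording

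*Protocol*

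**What the plan says.** **Doppler.** Section 5.1 states that measurements "of the umbilical and uterine arteries will be performed simultaneously with the remote eCTG for 24 patients", as clips of 2 x 5 minutes, in 12 women with PPROM and 12 with PE or FGR. Section 7.3.2 repeats the plan for inpatients (once per woman) and for outpatients (number of sessions not given). The Summary says that participation needs no additional fetal registrations.

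**Secondary outcomes.** Section 2.2 aims to "evaluate the interpretability of eCTG measurements throughout the hospital period". Section 7.1.2 lists the number of recordings, same-day repeats, switches for poor signal with their possible cause, and premature closures. Neither these sections nor 9.1 to 9.3 treat recordings with Doppler differently.

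**Device warning.** For the very small fetal ECG signal, section 6.4.4 says "it is recommended to avoid using equipment that emits electromagnetic radiation in the vicinity of these measurements".

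**Primary outcome.** Section 4.4: "Only the first day of remote eCTG measurements will be used for determination of the feasibility". Section 2.1 uses the first recording or, when indicated, "the second eCTG measurement on the first day of inclusion".

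**Day numbering.** Section 7.3.1 calls the day of identification the 1st day and continues: "After 24 hours (2 nd day) – when still eligible – patient will provide informed consent". Further on, the same section says of the Doppler subset: "From the second day onwards, for each inclusion, it is assessed whether the participant fits the aimed profile (section 5.1)".

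**The concern.** The study imitates self-administered home monitoring, with staff reached by app message and telephone. In a Doppler session someone holds a probe on the abdomen that carries the electrode patch. The protocol does not say who scans; I assume it is not the woman herself. That situation does not arise at home, yet the secondary success, repeat and switch results would include it and be read as home-like performance.

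The mixing is also uneven. Only women with PPROM, PE or FGR can contribute Doppler recordings, and section 9.2 plans subgroup analyses by those diagnoses. A recording that fails during a scan can lead to a repeat or a switch. Under 7.3.2 women stay on eCTG only while recordings succeed, so one failure may shorten a series.

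The second issue is timing. If the day on which Doppler may start were the day of inclusion, scanning could coincide with the recording that decides the primary outcome.

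**Working it through.** **1. The plan's own figures.** The Doppler subset is 12 + 12 = 24, and 24/60 = 40% of women. The 60 serves here only as a denominator. Its stated basis is "Calculated on 90% chance of success according Wilson standard error of proportions (CI95% > lower limit of 82.5%), 60 subjects are needed". A two-sided Wald calculation gives 1.96² x 0.9 x 0.1 / 0.075² = 61.5, so 62, close to 60. The named Wilson method has a two-sided lower limit of 79.9% at 54/60 and needs 99. That mismatch is a separate matter and does not affect this point.

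**2. Are the Doppler recordings scheduled ones?** Scanning is simultaneous with the remote eCTG (5.1, 7.3.2) and no additional registrations are made (Summary). They are therefore scheduled recordings, and they fall within the period that 2.2 and 7.1.2 cover.

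**3. Share of recordings.** Share = 24 / (60 x m), with one session per woman (stated for inpatients, assumed for outpatients). The number of recordings per woman, m, is not in the documents and is assumed.

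**4. Possible shift in the pooled success rate.** Shift = share x (0.90 − success rate with Doppler). The 90% is the planning value in 4.4. The rates with Doppler are assumptions.

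| m | Share | Shift if 80% with Doppler | Shift if 50% with Doppler |
|---|---|---|---|
| 2 | 24/120 = 20% | 2.0 points | 8.0 points |
| 5 | 24/300 = 8% | 0.8 points | 3.2 points |
| 14 | 24/840 = 2.9% | 0.3 points | 1.1 points |

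If success were higher with Doppler, the shift would go the other way.

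**5. Doppler time against the 20% limit.** Section 7.1.1 applies the limit to the recording overall. Take 2 x 5 = 10 minutes and, as an assumed worst case, complete signal loss during them and none otherwise: 10/30 = 33%, 10/50 = 20%, 10/90 = 11%. Doppler alone would then put any recording shorter than 50 minutes over the limit.

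**6. The second day.**
- Section 7.3.1: identification is day 1 and consent is day 2, and the same section then starts Doppler selection from the second day. Read literally, that can be the inclusion day.
- Section 7.3.2: the primary recording at inclusion comes first, then all later days, then Doppler from the second day. Read in order, that is the day after inclusion.

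The two readings allow from 0 to 24 of the 60 primary recordings to overlap with Doppler. At the upper bound, with an assumed 80% success under Doppler, the primary rate would be (24 x 0.80 + 36 x 0.90)/60 = 86% instead of 90%. Under the 7.3.2 order it is unchanged.

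**The case against.** **Timing.** Nothing can be done before consent, so if the second day meant the consent day the phrase would restrict nothing. It has content only as the day after inclusion, and 7.3.1 ties it to each inclusion. The 1st and 2nd day labels describe the reflection period. That section also lets women join a few days after admission, so it is not a study clock. The flowcharts, not shown, may settle the days. This largely stands. A reader might infer that up to 40% of primary recordings are exposed, but the documents do not support that as a realistic figure. What remains is that no sentence anchors the day.

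**Interference and help.** A reader might infer that 6.4.4 warns against ultrasound, or that an operator would improve the recording. The warning concerns equipment that emits electromagnetic radiation and does not name ultrasound. Nothing says that the person scanning assists with the eCTG. Testing whether simultaneous acquisition works is itself the additional objective. So neither harm nor benefit to the signal is established.

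**Existing safeguards.** Recordings can run to 90 minutes and be repeated, causes of poor signal are noted, and stored ultrasound clips (11.1) would identify the sessions. Section 9.2 anticipates sensitivity analyses without naming them, and the SAP, not shown, could separate these recordings. These reduce the harm. They do not change what the protocol's own outcome definitions include, and the start day is a conduct instruction that belongs in the protocol.

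**Conclusion.** The point holds for the secondary results. Followed as written, the protocol pools recordings made during Doppler in 24 of 60 women with self-administered recordings meant to reflect home use. With one session each, that is 20% of recordings at two per woman and 8% at five, both assumed. The documents give no success rate with Doppler, so the direction and size of any effect are unknown. The pooled effect is probably modest unless women contribute few recordings or success under Doppler is much lower.

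For the primary outcome the defect is one of wording: the start day is not explicitly tied to the primary recording, although the plainer reading protects it. Contamination of the primary success rate is not shown.

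**What to change.** 1. In 5.1, 7.3.1 and 7.3.2, replace the reference to the second day with: on any day after the day of the primary-outcome eCTG.
2. Flag each eCTG recorded with simultaneous Doppler.
3. Report the secondary success rate, repeats and switches from non-Doppler recordings as the main summary, and from all recordings as a sensitivity analysis. Split mechanically by the flag, not by a judgement of what Doppler triggered, which would need a causal call after the event.
4. Under 9.3, report signal loss with and without Doppler.

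The cost is a short wording change and one tick-box per recording. About 24 recordings leave the main secondary summary, for example 96 instead of 120 at two per woman or 276 instead of 300 at five. The flag cannot undo a series shortened after a Doppler recording, so that limitation should be stated with the results.

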## **5.2 Use of co-interventions**

Not applicable.

## **5.3 Escape medication**

Not applicable.

## 6. INVESTIGATIONAL PRODUCT

### 6.1 Name and description of investigational product(s)

Nemo Remote® (NRM) NI-fECG Nemo Healthcare (v1.2.6)

<https://a.storyblok.com/f/126579/x/afa5f256a9/nrm-techbro-eneu-v4-for-publishing.pdf>

When available, the most recent release will be used in this study. Technical brochure NRM is available on request at Nemo Healthcare B.V.; <https://nemohealthcare.com/en/contact/>

#### Introduction and system identification

Nemo Remote (NRM) system is a non-invasive and wireless medical device that accurately monitors fetal and maternal heart rate and uterine activity. Nemo Remote components, accessories and compatible devices can be identified in the table below.

[removed for publication]

*Figure 5. Nemo Remote® (NRM) system identification*

#### Operation

Nemo Remote Link – a wearable electronic measurement unit, and Nemo Patch – a passive self-adhesive electrode sensor, are used for recording of electrophysiological signals from the maternal abdominal surface. These recordings contain a mixture of signals including maternal electrocardiogram (ECG), fetal ECG, electrohysterogram (EHG), and various noise sources. The NRM Link is battery operated and is charged by docking it to Nemo Remote Link Charger.

Nemo Remote App utilizes advanced signal processing software, installed on a tablet, to suppress noise sources and separate maternal ECG, fetal ECG, and EHG. The first two signals are used to calculate maternal heart rate and FHR, respectively. The latter is used to calculate a measure for uterine activity. Recorded data is transferred between NRM Link and the tablet via a wireless connection which utilizes low-power 2.4GHz ISM frequency band. The app also serves as the primary user interface.

[figure not shown]

Figure 6. Nemo Remote® (NRM) patch, link, link charger and tablet app

#### Intended use

Nemo Remote® (NRM) is an electrophysiological measurement device that non-invasively measures FHR, uterine activity (UA) and maternal heart rate (MHR) from the fetal and maternal electrocardiography (ECG) and uterine electromyography (EMG) signals as acquired from abdominal surface electrodes. Nemo Remote® communicates to existing monitoring systems and is indicated for use on patients with a gestational age  $\geq 21$  completed weeks, with singleton pregnancies. The product is intended for use by patients in a home setting (prescribed by their HCP) and for use in non-acute care settings in a midwifery practice or hospital by HCPs.

### 6.2 Summary of findings from non-clinical studies

Not applicable.

### 6.3 Summary of findings from clinical studies

Not applicable.

### 6.4 Summary of known and potential risks and benefits

#### 6.4.1 Clinical benefits

Direct benefits There are no benefits directly from the system itself.

Indirect benefits

- In comparison to current remote monitoring devices (based on DU) Nemo Remote® can also be used from 21 to 32 weeks of gestation.
- In comparison to fetal monitoring in the hospital Nemo Remote® provides the possibility to be monitored at home.

- In comparison to current non-invasive fetal monitoring techniques (DU + TOCO) Nemo Remote® has a non-inferior performance and decreased maternal discomfort.

